A two-way mixed ANOVA will be used to assesses the effects of cueing modality and walk order on outcomes, i.e., cadence, gait speed, stride length, and CV_stride-time_. Comparable to the referenced PD study, cueing modality will be modelled as a within-subject factor, while walk order as a between-subject factor to account for potential sequence effects. For each outcome, within-participant changes from baseline will be calculated using cue-specific difference scores. To account for differences in scale and statistical distribution among the outcomes, change scores will be computed using Equations (30)-(31):

Percentage change of gait speed and stride length from baseline, calculated as:

$$\%\Delta =\frac{\text{Cue Value}-\text{Baseline Value}}{\text{Baseline Value}}\times \text{1}\text{0}\text{0}$$
(30)

In contrast,${\text{ CV}}_{\text{stride}-\text{time}}$, a dimensionless ratio-based variable that may have a skewed distribution, change will be computed using the natural log-ratio of cue value to baseline:

$$\Delta_{log}=\text{log}\left(\text{Cue Value}+\in \right)-\text{log}\left(\text{Baseline Value}+\in \right)$$
(31)

where 𝜖 is a small constant to avoid the logarithm of zero. This transformation was chosen as ${\text{CV}}_{\text{stride}-\text{time}}$ is a ratio-based measure that can be highly skewed and exhibit unequal variances across conditions. Applying the *log* transformation to change scores helps to normalise the distribution and stabilise the variance, thereby supporting more reliable statistical comparisons of cueing effects on ${\text{CV}}_{\text{stride}-\text{time}}$ in this within-subjects design. Post-hoc comparisons between cueing modalities will be conducted using paired t-tests, with Bonferroni correction applied to account for multiple comparisons. Effect sizes will be reported using Cohen’s d.

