If assumptions for normality are not met, a Friedman test will be used to assess within-subject differences across cueing conditions. Post-hoc Wilcoxon signed-rank tests, with Bonferroni correction, will be conducted only if the Friedman test is statistically significant. For between-subject effects (e.g., walk order), where normality assumptions are violated, the Kruskal–Wallis test will be used to assess group-level differences between walk-order groups. Interaction effects between cueing and walk order will be explored non-parametrically by conducting separate Friedman tests within each walk order group. Effect sizes for non-parametric tests will be calculated using the rank-biserial correlation coefficient, $\text{r}=\text{Z}/\sqrt{\text{N}}$, providing a measure of the magnitude of the effects observed.

For the three primary comparisons, we will control the familywise error rate using a Bonferroni adjustment. Given three cueing modalities, statistical significance (*p*) will be evaluated at a two-sided α = 0.01/3 = 0.0033. Effect sizes (i.e., SRM) and 95% confidence intervals will also be reported. Secondary and exploratory analyses (e.g., comparing cueing modalities to one another, examining washout effects, assessing stride-to-stride variability) will not be subject to multiplicity correction. For these analyses, a two-sided *p*-value of 0.05 will be considered statistically significant across all parametric and nonparametric tests.

To assess whether the first cue produced short-term residual effects, we will calculate changes in gait outcomes from baseline to each cued walk and from each cued walk to its subsequent washout walk (WO1 and WO2). For each cue exposure, a carryover score will be calculated as the difference between the change induced by the cue and the change observed during the corresponding washout period, reflecting retained cue effects. The approach enables an evaluation of carryover effects after each cued walk separately, thereby capturing any cumulative or progressive retention of cueing effects. Group differences based on initial cue type (i.e., counterbalanced sequence) will be evaluated using one-way ANOVA or the Kruskal–Wallis test, depending on normality assumptions [74–80].

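### The carryover score has no sign rule and, read literally, is highest when nothing is carried over; its only named test cannot show carryover common to all cues

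*Protocol article*

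**What the plan says.** The section on walking tasks places a washout after the first and second cued walks: a seated counting task, then a one-minute uncued walk. That walk is meant both to reset gait and to check whether anything from the cue persists. No washout walk follows the third cued walk.

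The Statistical analysis section gives the aim as: "To assess whether the first cue produced short-term residual effects". It then names the components, "changes in gait outcomes from baseline to each cued walk and from each cued walk to its subsequent washout walk (WO1 and WO2". It combines them by stating that a "carryover score will be calculated as the difference between the change induced by the cue and the change observed during the corresponding washout period", and describes the result as "reflecting retained cue effects". The only test named is this: "Group differences based on initial cue type (i.e., counterbalanced sequence) will be evaluated using one-way ANOVA or the Kruskal–Wallis test".

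The same section sets the direction of the article's other change scores: "within-participant changes from baseline will be calculated using cue-specific difference scores". Equation 30 is cue value minus baseline value, over baseline. Equation 31 is the log of the cue value minus the log of the baseline value. Both are later minus earlier. Neither is written out for the step from cued walk to washout walk. Washout effects are listed among the secondary and exploratory analyses, tested at a two-sided 0.05 without multiplicity correction.

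**The concern.** There are two separate difficulties.

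The first is the score. A measure of what is retained should be zero when gait returns to baseline and should rise as more of the cue effect persists. If the cue-to-washout change is signed later minus earlier, it is negative when the effect wears off. Subtracting it then adds the lost effect to the cue effect, where it should be taken off. Such a score falls as retention rises, and it depends on the size of the cue effect as well as on carryover.

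The second is the test. Comparing groups defined by first cue asks whether carryover differs between cues. It does not ask whether the first cue left anything behind.

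At stake is the evidence that the washout worked. Every cued walk is compared with a single baseline walk. With the three planned sequences of 20, each cue comes first in 20 participants and after another cue in 20 + 20 = 40. A carryover common to all cues would therefore enter the cue-versus-baseline estimates, and the washout walk is the direct place to see it. As written, complete washout could be reported as large retention, and a shared residual effect could pass unseen.

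**Working it through.** The plan states no figure on this point, so there is none to reproduce. The check is algebra on its definitions, plus a small simulation of the named test.

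**Inputs.** B, C and W are the walks named in the Statistical analysis section. D = C − B is the cue effect and r is the fraction retained, so W = B + rD and the true retained effect is W − B = rD. The values B = 100 and D = 10 are illustrative.

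**Three readings of the score.**
- Literal, both changes later minus earlier: (C − B) − (W − C) = 2C − B − W = (2 − r)D.
- Gain minus loss, washout change taken as the drop: (C − B) − (C − W) = W − B = rD.
- Washout change measured from baseline: (C − B) − (W − B) = C − W = (1 − r)D.

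| r | W | True W − B | Literal | Gain minus loss | Washout from baseline |
|---|---|---|---|---|---|
| 0 | 100 | 0 | 10 − (−10) = 20 | 10 − 10 = 0 | 10 − 0 = 10 |
| 0.5 | 105 | 5 | 10 − (−5) = 15 | 10 − 5 = 5 | 10 − 5 = 5 |
| 1 | 110 | 10 | 10 − 0 = 10 | 10 − 0 = 10 | 10 − 10 = 0 |

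Only the middle reading runs in the intended direction. For CV of stride time, where improvement is negative, the same holds in magnitude.

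**Scale.** The table uses one denominator. If each percentage change were taken on its own starting value, complete washout would be −10/110 = −9.1%. The literal score would then be 10 + 9.1 = 19.1, and even gain minus loss would give 10 − 9.1 = 0.9 where it should give 0. The article does not say which denominator applies to the washout step. For log-ratios the two steps add exactly to log W − log B, with the small constant carried in each term.

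**The test.** One-way ANOVA and Kruskal–Wallis respond only to differences between groups. If the same carryover c is added in all three sequence groups, every between-group difference is unchanged. This holds under any sign convention.

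**Simulation.** There were three groups of 20 with one washout walk each, alpha 0.05 and 4,000 runs. Assumed inputs, none of them from the article: gait speed 1.0 (SD 0.2), individual cue effect SD 0.10, measurement SD 0.05, and mean cue effect 0.10 except in the last row. The figures are rejection rates.

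| Scenario | ANOVA, literal score | ANOVA, W − B | One-sample test, W − B |
|---|---|---|---|
| No carryover, equal cue effects | 5.0% | 5.3% | 4.8% |
| Half retained for all cues | 4.6% | 4.3% | 99.2% |
| Fully retained for all cues | 5.2% | 4.6% | 100% |
| No carryover, cue effects 0.05, 0.10, 0.15 | 65.4% | 5.7% | 4.9% |

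The named test stays near 5% however large a common carryover is. In the last row nothing is carried over, yet the literal score is 2D, so the ANOVA detects the difference in cue effects and would label it carryover.

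**The case against.** The strongest reply is that the sentence describes gain minus loss. On that reading the score is W − B, which agrees with its stated purpose. The section gives an order of walks but no equation or sign rule for the washout step, and Equations 30 and 31 cover only cue against baseline. This stands. A reader might infer that the plan has fixed a reversed score; the text does not go that far. It permits a reversed score, and its literal wording with the article's own convention produces one. The denominator problem is likewise a possibility and not something the article states.

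A reader might also infer that the group test rejects at its alpha level whenever the three carryovers are equal. That is true of W − B. It is not true of the literal score, which also needs equal cue effects, as the last row of the simulation shows.

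Third, the analysis is secondary. No primary comparison or decision rule uses the score, walk order is a factor in the mixed ANOVA, and the Discussion says responses will be read in light of order and exposure and not as proof that one cue is superior. Each cue appears once in each position, so an equal additive carryover cancels in cue-versus-cue contrasts; differential carryover is the threat there, and the group test addresses it if the score is signed correctly. All this stands and limits the severity. It does not rescue the named test for the question asked, because an equal carryover does not cancel against baseline.

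Finally, the article is condensed, and a fuller analysis plan may say more. But this is not a gap left to another document: the article states a formula and a test, and the test does not match the stated aim.

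**Conclusion.** The point holds in two parts of different strength.

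- **Score.** It is ambiguous and, read literally, inverted: (2 − r)D, or 20, 15 and 10 for 0%, 50% and 100% retention of a 10-point effect. This is algebra and rests only on the later-minus-earlier convention. The gain-minus-loss reading gives the right quantity but is not stated.
- **Test.** Under either reading, a comparison by initial cue cannot show carryover common to all cues. This needs no assumption. The 99.2% and 65.4% figures depend on the assumed simulation inputs and only illustrate the contrast.

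It would go too far to conclude that the primary cue-versus-baseline comparisons are invalid. The article does not tie them to this score, and nothing in it shows that carryover will occur. This is a defect in a secondary analysis that should be corrected before that analysis is run.

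**What to change.** Replace the score with washout walk minus baseline walk: WO1 − NC and WO2 − NC. Express it as a percentage of the baseline value for gait speed and stride length (and for cadence, which the plan also reports as percentage change from baseline), and as the log-ratio to baseline for CV of stride time.

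Report the mean and 95% confidence interval over all participants and by preceding cue. Name WO1 − NC as the main estimate of the residual effect of the first cue. Keep the one-way ANOVA or Kruskal–Wallis test by sequence, applied to the new score and described as a check on differential carryover only.

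State two limits alongside. The baseline walk always comes first, so washout minus baseline also contains familiarisation and fatigue. WO2 − NC follows two cues and cannot be credited to one. In addition, no score exists for the cue given last, so each participant contributes two of the three cues.

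The cost is one formula and a few sentences. No new data are needed, since all the walks are already in the schedule.

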Therefore, the primary objectives of this protocol are to (i) validate gait characteristics from CuePD and (ii) evaluate the effects of personalised auditory cues (metronome beats, instrumental music, and vocal music) to retrain and improve gait in a lab, i.e., increase gait speed, cadence and stride length while reducing gait variability. Our secondary objectives are to assess recruited PwPD and their (a) acceptance and preference of personalised music cues compared to traditional metronome cueing while (b) understanding their ability to adhere to cues due to their musicality.

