**Fig 2 pone.0346508.g002:**
[figure not shown]
SPIRIT schedule of enrolment, interventions, and assessments. *Order of cued walks are allocated at enrolment.

(i)**Montreal Cognitive Assessment (MoCA)**: Administered as a screening tool to exclude those with cognitive impairment with <21 being a cut-off point for PwPD. The MoCA will be used as a standardised neuropsychological test acknowledged as a valid and efficient tool for the rapid screening of global cognitive dysfunction [63]. It is used to examine diverse cognitive domains including attention and concentration, executive functions, memory, language, visuo-constructional skills, conceptual thinking, calculations, and orientation.(ii)**Participant Demographics:** (a) Height and weight, (b) age, (c) ethnicity, (d) duration of PD diagnosis.(iii)**Education level**: (a) pre/post-high school, (b) college or (c) university(iv)**Physical activity levels**: To concisely capture physical activity across a range of habitual tasks, two questionnaires will be used: (i) a physical activity questionnaire for the elderly with a reference period of 1-year was used to understand functional household (e.g., cleaning) and community-based activities (e.g., shopping [64]), and (ii) the International Physical Activity Questionnaire Short Form (IPAQ-SF), to assess the types of intensity of physical activity and sitting time to estimate total physical activity in MET-min/week and time spent sitting [65].(v)**Falls history**: Falls incidence, cause, location and consequences in the previous 12-months will be assessed by a questionnaire based on recommendations [66,67], that leads with the question “In the past year, have you had any fall including a slip or trip in which you lost your balance and landed on the floor or ground or lower level?” [68].(vi)**Falls Efficacy Scale – International Version (FES-I)**: Used to measure fear of falling in the PwPD [68]. This short, validated measure will assess fear of falling during both basic and demanding activities (physical and social) using a scale from 1 (Not at all concerned) to 4 (Very concerned) across 16 scenarios.(vii)**MDS-Unified Parkinson's Disease Rating Scale (MDS-UPDRS)**: Commonly employed to evaluate both motor and non-motor symptoms associated with PD [69]. This scale consists of four main sections, each targeting a specific area of evaluation. The first part examines non-motor experiences that occur during daily living, while the second part assesses motor experiences during daily living. The third part evaluates motor examination, while the fourth part focuses on assessing complications related to therapy. To determine the severity of the symptoms, the UPDRS is scored based on a total of 195 points, where higher scores suggest increasing levels of disability.

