#### Adherence to cues and musicality.

Adherence will be treated both as a continuous variable (percentage change in cadence from baseline) and as a binary variable for group comparisons. The primary binary adherence definition is: adherent = ≥5% increase in cadence from baseline; non-adherent = < 5%. Mann–Whitney U tests will compare Gold-MSI between adherent and non-adherent participants. Participants with missing baseline or intervention-based cadence (e.g., wishing to withdraw or technology failure) will be excluded from binary adherence analyses and numbers excluded will be reported.

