To evaluate the relationship between musical sophistication and response to cueing, two sets of analyses will be conducted using Gold-MSI subscale scores. Assumption checks, including the Shapiro-Wilk test and Q-Q plot inspections, will be used to assess the distribution of change scores prior to both analyses. First, the association between Gold-MSI scores and cue adherence (defined as the absolute deviation from a + 10% target increase in cadence) will be assessed using Spearman’s rank correlation coefficient, with Bonferroni correction for multiple comparisons across subscales. Second, associations between Gold-MSI scores and gait outcome improvements (percentage change in gait speed and stride length, and log-ratio change in ${\text{CV}}_{\text{stride}-\text{time}}$) will also be tested using Spearman’s correlation, with Bonferroni correction.

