### Exploratory objectives: preference, usability, and musicality

Exploratory objectives of the protocol also focus on the user experience and the clinical efficacy of the personalised auditory cues provided by CuePD. A significant part of this exploration involves understanding the preferences of PwPD for engaging with personalised music cues during routine walking exercises, compared to traditional metronome cues which are often perceived as monotonous and less engaging. This preference for music could play a crucial role in enhancing patient engagement and adherence to the rehabilitation process. Finally, the study explores how well patients’ musicality correlates with their ability to synchronise with the auditory cues. If no relationship is found, this would indicate that the success of music cueing-based interventions does not depend on a patient's inherent musical skills, potentially broadening the applicability of such treatments to a wider demographic of PwPD.

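### The Gold-MSI analyses are unadjusted, so they describe an association and do not support the causal-type statements made about musicality

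*Protocol article*

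**What the plan says.** Three analyses in the Protocol article serve the musicality objective.

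- **Musicality and adherence (Statistical analysis).** Adherence is "defined as the absolute deviation from a + 10% target increase in cadence". It is related to Gold-MSI scores by Spearman's "rank correlation coefficient, with Bonferroni correction for multiple comparisons across subscales".
- **Musicality and gait gain (Statistical analysis).** Percentage change in gait speed and stride length, and log-ratio change in stride-time CV, are tested by Spearman's "correlation, with Bonferroni correction".
- **Binary adherence (Adherence to cues and musicality).** With a cut at a 5% rise in cadence, Mann–Whitney "U tests will compare Gold-MSI between adherent and non-adherent participants".

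No covariate, partial correlation, regression or stratification is named for any of them.

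The Data collection section lists age, disease duration, MoCA and MDS-UPDRS among the items taken before the gait tasks. MDS-UPDRS is described as "Commonly employed to evaluate both motor and non-motor symptoms associated with PD", and of its sections, "The third part evaluates motor examination". MoCA serves as a screen. No planned analysis uses any of these as a covariate.

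Two passages go beyond association. Secondary objective (b) in the Introduction is worded as "understanding their ability to adhere to cues due to their musicality". The Discussion, under Exploratory objectives, says of a finding of no relationship that "this would indicate that the success of music cueing-based interventions does not depend on" the patient's own musical skill, and links this to wider use.

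**The concern.** Musicality is a characteristic of the person and cannot be assigned. The counterbalanced crossover protects comparisons between cues within a person, but not comparisons between more and less musical people. Bonferroni controls multiplicity, not confounding. Change from baseline removes fixed differences in gait level, but not differences in the ability to respond to a faster beat.

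That ability could depend on motor severity, cognition and age, and so could answers to a self-report on musical engagement, perception and singing. The sample leaves room for variation: age has no upper limit from 50, and MoCA can run from 21 to 30. A common cause could therefore produce an association where musicality has no effect, or mask one that exists. At stake is whether objective (b) and the planned reading of a null result can be stated as they are worded.

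**Working it through.** The protocol gives no figure for the musicality analysis, so there is none to reproduce. The question is how much an unadjusted rank correlation could mislead.

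**Inputs from the protocol**
- Analysed n: 60 recruited with up to 10% attrition gives 60 × 0.90 = 54.
- Significance level: 0.05 for secondary and exploratory analyses, and five Gold-MSI subscales, so 0.05/5 = 0.01. If the general score or the three gait outcomes are also counted, the level is stricter.
- Adherence outcome: absolute deviation from +10%.

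**Assumed inputs (the documents give none)**
- One confounder C, with correlation a to musicality and b to response, and no true effect of musicality.
- For the absolute-deviation outcome: SD of cadence change 5 points, mean change 5%, 7% or 10%.

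**Step 1: the spurious correlation.** With no true effect, the correlation induced between musicality and response is a × b:
- 0.2 × 0.2 = 0.04
- 0.3 × 0.3 = 0.09
- 0.3 × 0.4 = 0.12
- 0.4 × 0.5 = 0.20

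The critical correlation at n = 54 is t/√(n − 2 + t²), which is 0.268 at 0.05 and 0.348 at 0.01.

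**Step 2: false-positive rate, directly related outcome** (simulation, n = 54)

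| a / b | at 0.05 | at 0.01 |
|---|---|---|
| 0.2 / 0.2 | 6% | 1.5% |
| 0.3 / 0.3 | 10% | about 3% |
| 0.3 / 0.4 | 13% | about 4% |
| 0.4 / 0.5 | 28% | about 11% |

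The partial rank correlation, (r_MY − r_CM·r_CY)/√((1 − r_CM²)(1 − r_CY²)), rejects in about 5% and 1% throughout.

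**Step 3: the planned adherence outcome.** If the confounder acts on cadence change, taking the absolute deviation from +10% folds the variable and weakens the link. Rates at 0.01:

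| a / b | mean change 5% | 7% | 10% |
|---|---|---|---|
| 0.3 / 0.4 | 3.4% | 1.9% | 1.1% |
| 0.4 / 0.5 | 7.9% | 4.3% | 1.0% |

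If participants reach the target on average, the bias on this measure all but vanishes. Folding does not apply to the gait-gain correlations. The 5% split was not simulated.

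**Step 4: masking.** Take a direct effect of 0.3 with opposing paths of 0.4. The unadjusted correlation is 0.3 − 0.4 × 0.4 = 0.14. In simulation the mean Spearman is 0.13, with 15% power at 0.05. The partial correlation averages 0.26, with 48% power.

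**Step 5: what a null can show.** With no confounding at all, a true correlation of 0.3 is detected in only about 31% at 0.01. By Fisher's z, an observed correlation of zero has a 95% interval of ±tanh(1.96/√51) = ±0.27. Adjustment does not change this.

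**The case against.** The best defence is that the analysis is mostly described as one of association: the Abstract, the Gold-MSI item and the Statistical analysis section speak of a relationship or association. Spearman estimates that properly. For the practical question of whether less musical patients can use the cues, the unadjusted association is arguably the relevant quantity. This stands, and it is why the unadjusted values should be kept. It does not cover objective (b) or the planned reading of a null.

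The aim is also called exploratory in the Discussion (secondary in the Introduction), and no primary result depends on it. That limits the weight. Adjusted sensitivity analyses are often left to a full analysis plan, but here the article itself fixes the method and the conclusion to be drawn.

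Two stronger readings are tempting. One is that the musicality tests carry a false-positive rate of 13% to 28%. Those figures hold at 0.05, whereas the correlations are Bonferroni-corrected, and every confounder strength behind them is assumed. The other is that only the adjusted result should count. The documents do not settle whether MoCA is a confounder or partly a consequence of musical background, in which case adjusting for it could remove real effect. Adjustment would not rescue the null inference either, as Step 5 shows.

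**Conclusion.** The point holds in a limited form. The planned Gold-MSI analyses are unadjusted although plausible common causes are recorded, so they do not support a statement that adherence is due to musicality or that success does not depend on it.

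The documents do not show that the association will be biased, by how much, or in which direction. At the level of about 0.01, the range is about 1.5% to 11% for a directly related outcome and about 1% to 8% for the absolute-deviation measure. Both rest on assumed confounder correlations, and the second also on an assumed mean and SD of cadence change. With confounding of about 0.2 on each path, the rate is close to nominal. The null inference fails on precision as well as on confounding.

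This is worth correcting because the conclusion is written in advance and the data are already being collected. It does not touch the primary objectives.

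**What to change.** 1. Prespecify partial Spearman correlations adjusted for MDS-UPDRS Part III, MoCA and age, reported beside the unadjusted ones for both adherence and gait gain.
2. Add a matching adjusted analysis to the Mann–Whitney comparison, for example a logistic regression of binary adherence on Gold-MSI with the same covariates. Because one adherence group may be small, name a fallback in advance.
3. Give confidence intervals for every estimate, and discuss any difference between adjusted and unadjusted values rather than declaring one decisive.
4. Reword objective (b) in the Introduction as an association between musicality and adherence. Reword the Discussion so that a non-significant result is reported with its interval and is not read as showing that success does not depend on musical skill.

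The cost is about three degrees of freedom (52 become 49 at n = 54), a little more analysis and a few lines of text. No new data are needed. Adjustment covers only the measured factors, so residual confounding should be acknowledged.

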
After completion of all walks, participants will complete:

(viii)**Goldsmiths Musical Sophistication Index (Gold-MSI)**: A 39-item (scored from 1 to 7) self-report designed to assess musicality across five subscales: active engagement (AE), perceptual abilities (PA), musical training (MT), singing abilities (SA), and emotional response (ER) to music [70]. This tool evaluates and provides the detailed extent and nature of musical experiences and skills, but also provides a broader score on musicality, General Music Sophistication (GMS), ranging from 32 to 126. For this study, the scale will be used to assess if there was a relationship between an individual’s general music sophistication and their adherence to the beat of the music cues. Furthermore, the relationship between an individual’s subscale results and beat adherence will also be assessed.(ix)**System Usability Scale (SUS):** This will evaluate perceptions of the app’s usability, complexity, and overall satisfaction [71]. The SUS produces a composite score that ranges from 0 to 100, calculated by first adjusting the responses from a set of ten questions. For odd-numbered questions, the process involves subtracting one from each score, whereas for even-numbered questions, the score is subtracted from five, resulting in adjusted values that fall between 0 and 4. These adjusted values are subsequently summed together, and the total is multiplied by 2.5 to derive the final SUS score, with higher scores reflecting superior usability.(x)**Cueing preference:** Lastly, participants are asked a question to determine preferred cueing modality, “Which cueing do you prefer, was it metronome, instrumental music or vocal music?”

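### Musicality and cue adherence (secondary objective b) is tested in several ways at conflicting thresholds, with two adherence definitions and no test named as deciding

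*Protocol article*

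**What the plan says.** All references are to the protocol article.

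- **Introduction.** Secondary objective (b) concerns participants' ability to adhere to cues in relation to their musicality. The Discussion lists the same topic under exploratory objectives.
- **Data collection, item (viii).** The Gold-MSI is to be used for the relationship between an individual's "general music sophistication and their adherence to the beat of the music cues". The five subscales come after this, as a further question.
- **Statistical analysis, Gold-MSI paragraph.** Here "two sets of analyses will be conducted using Gold-MSI subscale scores". The first set correlates Gold-MSI scores with adherence, defined as absolute deviation from a 10% cadence increase, using Spearman's coefficient "with Bonferroni correction for multiple comparisons across subscales". The second set relates the scores to gait change ("percentage change in gait speed and stride length, and log-ratio change in" stride-time variability). These "will also be tested using Spearman’s correlation, with Bonferroni correction", with no number of tests given.
- **Adherence to cues and musicality.** Adherent means a cadence rise of at least 5%. On that split, "Mann–Whitney U tests will compare Gold-MSI between adherent and non-adherent participants". The section does not say which Gold-MSI score or which cue is used, and it states no correction.
- **Statistical analysis, multiplicity paragraph.** Secondary and exploratory analyses "will not be subject to multiplicity correction", and a two-sided p-value of "0.05 will be considered statistically significant across all parametric and nonparametric tests".
- **Statistical analysis, cue adherence.** Percentage change in cadence is calculated from baseline to each cueing modality, which gives three values per participant.

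**The concern.** One objective has several candidate tests, and they differ in three respects: the musicality score (general or subscale), the adherence definition (distance from target or a 5% threshold) and the p-value needed (0.01 or 0.05). Nothing says which result answers the objective. A p-value of 0.03 for a subscale against adherence is not significant under the Bonferroni step but is significant under the general rule. The same p-value from a Mann–Whitney test is significant with no correction at all. A report could therefore claim a musicality effect from whichever score, cue or test crosses its own line.

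The opposite error matters too. The Discussion says that finding no relationship would indicate that music cueing does not depend on musical skill, which would widen its applicability. Spreading alpha over the subscales weakens the plan's ability to detect a relationship, and so weakens that inference.

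**Working it through.** The article states no error rate or power for this objective, so there is no figure of its own to reproduce.

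**1. Do the two adherence definitions agree?** Take three participants:
- Cadence change 0%: deviation |0 − 10| = 10 points; below 5%, so non-adherent.
- Cadence change +10%: deviation 0; adherent.
- Cadence change +20%: deviation |20 − 10| = 10 points; at least 5%, so adherent.

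The first and third are equally far off target in the correlation but fall in opposite groups in the Mann–Whitney test. The two analyses can point in different directions.

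**2. How many adherence correlations are there?** Five subscales (Data collection) and three cues (Walking/gait tasks) give 5 × 3 = 15 tests if the correlations are run per cue. The article does not say so outright; it follows from adherence being calculated per cue. The stated correction counts five: 0.05/5 = 0.01 per test.

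**3. Chance of at least one false result, independent tests.**
- One cue or a cue average: 1 − 0.99^5 = 4.9%. The correction works for the family it names.
- Three cues: 1 − 0.99^15 = 14.0%.
- Three cues plus three Mann–Whitney tests on the general score at 0.05: 1 − 0.99^15 × 0.95^3 = 26.3%.
- Cues averaged, plus one Mann–Whitney test on the general score: 1 − 0.99^5 × 0.95 = 9.7%.

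**4. Allowing for correlated tests.** The article gives no correlations, so these are assumptions. Trials were simulated under no association, 4,000 per setting, with 60 participants, cadence change of mean 6% and SD 5%, and the general score taken as the sum of the subscales.

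| Correlation among subscales / among cues | Adherence correlations only | With Mann–Whitney on general score |
|---|---|---|
| 0.3 / 0.3 | 13.0% | 22.5% |
| 0.5 / 0.5 | 11.8% | 19.6% |
| 0.5 / 0.7 | 11.9% | 20.4% |
| 0.7 / 0.8 | 9.4% | 17.3% |

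A second set of assumptions (54 participants, mean 7%, SD 4%, correlations 0.3 to 0.8) gave 10–14% for the adherence correlations alone.

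**5. Power for a true correlation of 0.3.** The value 0.3 is an assumption. With 10% attrition, n = 60 × 0.9 = 54. The Fisher z approximation for Spearman gives power = Φ(atanh(0.3) × √[(54 − 3)/1.06] − z), where 0.3095 × 6.936 = 2.147.
- One named test at 0.05: Φ(2.147 − 1.960) = 57%.
- At 0.01: Φ(2.147 − 2.576) = 33%.
- Fully corrected over 15 tests (0.05/15 = 0.0033): Φ(2.147 − 2.935) = 22%.

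**The case against.** Musicality is secondary, or exploratory by the Discussion, and the article claims no familywise control over it. The Bonferroni step controls the family it names, the subscales. Per-cue testing is inferred, and family sizes are a detail that an article may leave to a fuller document. The general score is planned in Data collection, and the Gold-MSI paragraph, after opening with subscale scores, goes on to speak of Gold-MSI scores, so this may be loose wording. A specific correction might also be read as overriding the general no-correction rule.

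Much of this stands. It limits the severity and makes the 14.0% conditional on per-cue testing. It does not remove the defect: what the article itself fixes (scores, definitions, tests and thresholds) does not fit together, and no statement says that the specific rule prevails.

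A reader might go further and infer that a false musicality finding is more likely than not. The documents do not support that. A figure above one half needs one of two readings that the text does not state:
- The gait-outcome correction also counts subscales only: 1 − 0.99^60 × 0.95^3 = 53.1% with independent tests.
- Uncorrected Mann–Whitney tests are run on every subscale and cue: 1 − 0.95^15 = 53.7%.

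The subscale-only wording attaches to the adherence correlations alone. If the gait correction covers all 5 × 3 × 3 = 45 of its tests, the whole set with Mann–Whitney on the general score gives 1 − 0.99^15 × (1 − 0.05/45)^45 × 0.95^3 = 29.9% with independent tests. Nor are gait-outcome correlations part of objective (b), which concerns adherence.

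**Conclusion.** The point holds as an inconsistency worth correcting. Objective (b) has no deciding test, the score in the analysis differs from the score in the stated question, the two adherence definitions can conflict, and the general multiplicity rule contradicts the Bonferroni step.

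If the correlations are run per cue and the Bonferroni text governs, the chance of at least one false adherence correlation is 14.0% for independent tests and about 9–14% under the assumed correlations. With Mann–Whitney tests on the general score added, it is about 17–26%. No single figure for the whole musicality set can be given, because the scope of the gait-outcome correction is not stated. The consequence is confined to how a musicality result, positive or null, can be read.

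**What to change.** Name one score, one adherence definition and one cue handling as the deciding test for objective (b), at two-sided 0.05, before the Gold-MSI data are analysed. One option that follows the question in Data collection is the Spearman correlation of the general score with absolute deviation from +10%, averaged over the two music cues. Averaging is not required. Including the metronome would also be defensible, since the Introduction speaks of cues in general, provided the choice is stated.

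Then do one of the following:
- Label the subscale, per-cue, gait-outcome and Mann–Whitney results descriptive and report them with intervals.
- Keep significance claims for the subscales, correct over all subscale-by-cue tests, and accept the lower power (22% rather than 57% in the example above).

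State the number of tests in each Bonferroni step, including the gait-outcome one. Reconcile the Gold-MSI item in Data collection, the section on adherence and musicality, and the multiplicity and Gold-MSI paragraphs of Statistical analysis.

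The cost is wording only; no further data are needed. With the first option, subscale and per-cue results no longer carry a significance claim. In return, the deciding test has a 5% error rate and, for a true correlation of 0.3 with 54 completers, 57% power against 33% at the 0.01 level.
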